### Primary and secondary outcomes

The primary outcome is the return of an adequate test kit in all randomised participants (intention-to-treat analysis). Return of an adequate test kit will be defined as return of a gFOBt kit within 18 weeks of the invitation with a ‘definitive’ test result of either ‘normal’ (i.e. no further investigation required) or ‘abnormal’ (i.e. requiring referral for further testing, usually colonoscopy). Identification of individual-level mobile number registration on the GP Clinical System will constitute an important secondary outcome measure. Thereby, in order to test the efficacy of text-message reminders in CRC, we will limit the comparison of the effectiveness of a text reminder to those who have a registered mobile number on GPs Clinical System and have not returned their test kit within eight weeks (per-protocol analysis).

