### Timeline

On the seventh week of each screening episode, all individuals invited to CRC screening from the participating GPs will be enrolled into the study and randomised to stay in the study for another eleven weeks until their screening episode is closed for gFOBt participation (excludes colonoscopy participation).

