### Blinding & randomisation

Individuals registered at participating GP will not be informed that they are participants in a research study, and the study investigators will not know which individuals have been assigned to the intervention or control groups until the end of the trial when all data have been collected and anonymised. Randomisation of individuals to study groups will be handled by iPlato using simple pseudo-random allocation methods stratified by the preselected CCGs. Individuals will be randomised in a 1:1 ratio to either the intervention or control condition after 7 weeks of their screening episode irrespective of whether or not they have a mobile number registered on their GP’s Clinical System.

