**Fig. 3 Fig3:**
[figure not shown]
TRICCS Data Processing Diagram

IdentificationOn a weekly basis, the Hub will identify eligible patients who are seven weeks into a screening episode. Eligible individuals will be those who have not opted-out of screening and who are registered with participating GP practices.Data ProcessingIn the same week as the identification, iPlato will link data from the GP Clinical System with the Hub’s information system to randomise people into intervention and control groups. Data will be matched by via patient NHS Numbers (a unique ten digit identifier). By linking the data between these two systems, iPlato will be able to identify individual-level screening episode data (return of test kit by the end of Week 7) from the Hub and individual’s mobile telephone number from the GP Clinical System. In order to have the best real life representation of overall screening uptake (intention-to-treat), all individuals with or without a mobile number are included in the study. iPlato will be using a secure NHS server (‘N3’) to bring the data together under one network. The iPlato system updates itself every 4 h, thereby removing in real time any individual from the trial who becomes removed from the GP system (e.g. due to reasons such as death or patient relocation).Data GenerationAfter 8 weeks of an individual’s screening episode, patients in the intervention group who have not returned their test kit and who have a mobile number stored on the GP Clinical System will be sent the text-message reminder. iPlato will generate several additional variables in response to this process, including: 1) whether a mobile record was available or not; 2) whether the individuals had already returned their test kit, and thereby whether a text-message was attempted; and 3) whether the text-message was successfully delivered or whether it failed (i.e. if the individual had an inactive mobile). Data Generation will be an on-going procedure each week until the sample size requirement is met.Data MergeOnce data collection is complete, iPlato will remove the mobile numbers and return the data to the Hub electronically through a secure N3 network connection. The Hub will add to the dataset whether the individual was adequately screened (yes/no) at the end of their individual episode (end of week 18), and then merge the dataset with any other variable that was not required by iPlato, but is useful for the purposes of the analysis (i.e. age, gender, episode number, social deprivation score, and adequately screened). The data merge will be a one-off procedure.AnonymisationThe researchers do not form part of the usual care team and as such will not have access to patient identifiable data at any point in the study. The Hub will remove all identifiable information from the dataset prior to analysis by the research team. Date of birth (DOB) will be converted into age at invite, gender encrypted using binary measures (i.e. 1 male, 2 female), and individual NHS numbers removed. Postcodes will be converted into scores based on census derived indicators of deprivation - i.e. the Index of Multiple Deprivation (IMD) [24]- and then removed from the dataset. As it is not required for analysis, the individuals GP code will be removed; however, the individuals CCG will be retained and will constitute one of the variables included in the multivariable analysis.ExtractionThe anonymised dataset will be sent to the principal investigator.DeletionOnce the data have been extracted, anonymised, and transferred, the research team will confirm that the data collection process has been completed and that iPlato’s records of the data should be destroyed. The Hub will retain the anonymised data for three months and the researchers will store the anonymised data for 10 years.

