### Statistical analysis

The primary and secondary outcomes will be analysed using a univariable logistic regression model, and then adjusting for age, gender, IMD score, CCG and episode number (first episode vs incident episode) in a multivariable model. Sample characteristics will be reported using descriptive statistics. The comparison of overall uptake between trial arms will be presented using odds ratios (ORs) and 95 % confidence intervals (CIs).

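### The primary comparison ignores week-7 kit status, a strong baseline predictor held for everyone at randomisation, and so carries avoidable noise

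*Protocol article*

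**What the plan says.** Under Timeline, enrolment covers everyone invited: "On the seventh week of each screening episode, all individuals invited to CRC screening from the participating GPs will be enrolled into the study". Nothing limits it to people whose kit is still outstanding. Under Blinding & randomisation, allocation is 1:1, "irrespective of whether or not they have a mobile number registered on their GP’s Clinical System". The message itself goes only to "patients in the intervention group who have not returned their test kit and who have a mobile number stored on the GP Clinical System" (Data processing and data collection, the Data Generation step).

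The primary outcome is analysed in everyone: "The primary outcome is the return of an adequate test kit in all randomised participants (intention-to-treat analysis". The reason for including people without a mobile is given in the Data Processing step: "In order to have the best real life representation of overall screening uptake (intention-to-treat), all individuals with or without a mobile number are included". This matches the primary aim, which is total uptake in the population. No reason is given for leaving prior kit return out of the comparison.

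The same step says that the provider links "individual-level screening episode data (return of test kit by the end of Week 7) from the Hub and individual’s mobile telephone number" when it randomises. Statistical analysis then fixes a univariable logistic model followed by one "adjusting for age, gender, IMD score, CCG and episode number (first episode vs incident episode) in a multivariable model". Kit status at week 7 is in neither.

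Primary and secondary outcomes already plans a secondary comparison, labelled per-protocol, limited to people with a registered mobile whose kit had not come back within eight weeks.

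**The concern.** A person whose kit came back before the end of week 7 cannot be prompted by a message sent after week 8. Such people add nothing to the treatment contrast. In an unadjusted comparison, though, a chance difference between arms in their number passes straight into the estimated effect. Randomisation makes that difference zero on average, so the estimate is unbiased, but its variance is larger than it need be.

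The status is recorded before any message goes out and in the same way in both arms, so conditioning on it respects the randomisation. It should also predict final uptake much better than age, gender, deprivation score, CCG or episode number, because an early return nearly determines the outcome. What is at stake is precision: a real but modest effect is more likely to be missed than the data require.

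**Working it through.** **Plan's own figure.** Inputs from Sample size calculation: control uptake p = 0.4351, gain g = 0.05, two-sided 5% level (sidedness is not stated, but two-sided reproduces the figure), 80% power. The two-proportion formula gives 1559 per arm, or 1599 with continuity correction. The stated 1600 is therefore right for a 5-point gain over everyone randomised.

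**Unadjusted comparison, n = 1600 per arm.** SE = √{[p(1−p) + (p+g)(1−p−g)]/n} = √{[0.2458 + 0.2498]/1600} = 0.01760. Power = Φ(0.05/0.01760 − 1.96) = Φ(0.88) = 81%. For g = 0.02 the SE is 0.01757 and power is Φ(1.14 − 1.96) = 21%.

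**Comparison stratified by week-7 kit status, same people, same population target.** Two inputs are assumptions, as the document gives neither:
- r, the share with a kit back by the end of week 7: 10%, 25% or 35%.
- a, the share of those kits that end as adequate: 97%, with 100% as the limiting case. A value below 100% allows for spoilt, failed or unclear kits, which the usual-care pathway says lead to a repeat kit.

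Among people not yet returned, control uptake is c = (p − a·r)/(1−r) and intervention uptake is t = c + g/(1−r). The population gain is therefore still g. The share-weighted stratified difference has

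SE = √{[2r·a(1−a) + (1−r)(c(1−c) + t(1−t))]/n}.

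Example with r = 0.25, a = 0.97, g = 0.05: c = (0.4351 − 0.2425)/0.75 = 0.2568 and t = 0.2568 + 0.0667 = 0.3235. SE = √{[0.0146 + 0.75(0.1909 + 0.2188)]/1600} = 0.01418. Power = Φ(0.05/0.01418 − 1.96) = Φ(1.57) = 94%.

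| r | SE, 5-point gain (a = 97%) | Power, 5-point gain: a = 97% / 100% | Power, 2-point gain: a = 97% / 100% |
|---|---|---|---|
| none used (plan) | 0.01760 | 81% | 21% |
| 10% | 0.01654 | 86% / 86% | 23% / 23% |
| 25% | 0.01418 | 94% / 95% | 30% / 32% |
| 35% | 0.01159 | 99.1% / 99.7% | 44% / 51% |

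Simulating the standardised difference and a Mantel-Haenszel test (20,000 trials per cell) agreed with these figures to within about half a percentage point.

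The ratio of squared standard errors at a = 97% shows the variance falling by about 12% (r = 10%), 35% (r = 25%) and 57% (r = 35%).

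**What stratifying does not do.** Stratifying everyone by kit status and mobile registration together does not reach the power of a test confined to non-returners with a mobile. For a 2-point population gain, with all early kits adequate and 39.8% mobile coverage (the figure cited in the Discussion), the stratified Mantel-Haenszel test has 32%, 38% and 52% power at r = 25%, 30% and 35%. The confined test has 64%, 72% and 84%. People without a mobile keep their weight in the stratified test, as the population target requires.

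**The case against.** The strongest reply is that the primary population follows from the primary aim. A programme deciding on roll-out with incomplete mobile records needs the effect on overall uptake, and comparing everyone randomised estimates that directly. This stands. A reader might infer that including people without a mobile is an error, or that the primary test should move to people the text can reach. The document does not support either. Including them is explained, and the restricted comparison is already the secondary analysis. Making it primary would change the question. Scaling its result back to the population would also need the assumption of no effect on anyone outside the stratum.

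It can also be said that early outcomes are not wholly fixed, because a returned kit may be spoilt and repeated. That is right, and it is why the working uses 97% as well as 100%. The gain shrinks slightly and does not disappear.

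A third point is that the size rests on an early-return share the document does not give, and that at the planned 5-point effect the trial already meets its 80% target. Both are true. The gain is modest if the share is near 10%. None of this is a reason to leave the variable out, since using it keeps the population, the target and the randomisation as they are.

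**Conclusion.** The point holds as a matter of efficiency. There is no bias, no contradiction and no error in the stated sample size. The primary analysis omits a baseline variable that the provider holds for everyone and that largely determines the outcome for those who have already returned. Using it would raise power for the planned 5-point gain from 81% to about 85–86%, 94–95% and 99% or more at early-return shares of 10%, 25% and 35%. For a 2-point gain it would rise from 21% to about 23%, 30–32% and 44–51%.

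These figures assume those shares, that 97% to 100% of early kits end as adequate, and no effect of the text on people whose kit is already back. The direction does not depend on the exact share, but the size does.

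**What to change.** - Keep all randomised participants as the primary population and overall uptake as the target.
- Stratify or standardise the primary comparison by kit returned by the end of week 7 (yes/no). Mobile registration may be added as a further baseline covariate.
- Report the all-randomised difference in uptake with its 95% CI beside the odds ratio. Standardising is preferable to simply adding kit status to the logistic model. The odds ratio cannot be expected to be the same in returners and non-returners, and near-complete adequacy among early returners can make the model unstable.
- Keep the comparison in mobile-registered people who have not yet returned as the planned secondary analysis, and do not present it as equivalent to the stratified test.

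The cost is a change of analysis wording before the data are seen, with no extra participants or data collection. The one practical step is to make sure that week-7 status, for both arms, is kept in the file passed to the Hub and on to the researchers, because the provider's records are destroyed after extraction.

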### Statistical analysis

The primary and secondary outcomes will be analysed using a univariable logistic regression model, and then adjusting for age, gender, IMD score, CCG and episode number (first episode vs incident episode) in a multivariable model. Sample characteristics will be reported using descriptive statistics. The comparison of overall uptake between trial arms will be presented using odds ratios (ORs) and 95 % confidence intervals (CIs).

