### Invitation

#### The NHS Bowel Cancer Screening Programme Pathway (Usual Care Group)

At age 60, and then biennially up to and including the age of 74, adults registered with a GP in England (who have not explicitly opted out of the screening programme) are sent an invitation letter and information booklet by their local Hub notifying them that they will soon receive a test kit as part of a national screening programme for CRC. A gFOBt kit and instructions follow 8–10 days later; the individual is asked to collect samples from three consecutive bowel motions and to then return the completed kit to the Hub in a pre-paid envelope for processing. Repeat gFOBt kits are sent out where the returned kit has been completed improperly (a ‘spoilt kit’), where there is a technical failure in processing the kit or where there is an unclear result. A reminder letter is sent out after four weeks after the initial invitation. If thirteen more weeks pass with no response, the screening episode is closed (i.e. after 18 weeks) and the individuals practice receives a letter of notification regarding their non-participation in the programme. If the test results are abnormal, a referral is made to the local screening centre for further investigation.

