
### Sample size calculation

The study has been designed to detect a 5 percentage point increase in uptake between the intervention and control groups. The expected uptake of CRC screening in the control group (43.51 %) was based on the uptake in the selected CCGs in London between May and October 2014. The anticipated improvement in uptake in the intervention group (5 percentage points, to 48.51 %) was based on the results from similar studies evaluating the effectiveness of text-message reminders to facilitate uptake in other areas of healthcare [12]. To detect this increase in uptake with 80 % power and 5 % significance level, 1600 participants per trial arm are required, giving a total sample size of 3200 participants.

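### Screening history is coded only as first versus an undefined 'incident' episode, and the single Hub merge lists no earlier-response field, so the adjusted analysis gives up some power and description

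*Protocol article*

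**What the plan says.** The Statistical analysis section of the protocol article specifies a univariable logistic regression followed by a multivariable one, "adjusting for age, gender, IMD score, CCG and episode number (first episode vs incident episode"), with results given as odds ratios and 95% confidence intervals. The term 'incident' is not explained.

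Under Data processing and data collection, the Data Merge step names what the Hub will add to the analysis file: "i.e. age, gender, episode number, social deprivation score, and adequately screened". The last item is the result of the current episode. The merge is done once. NHS numbers are then removed, and iPlato's records are destroyed after transfer.

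Two other sections show who will be in the trial. Invitations go out "At age 60, and then biennially up to and including the age of 74" unless the person has opted out. The Timeline section says that "all individuals invited to CRC screening from the participating GPs will be enrolled into the study". Neither excludes people who ignored earlier invitations.

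**The concern.** Invitations at 60, 62, and so on to 74 make eight rounds, so many participants will be past their first. With expected control uptake below one half, many of these will not have returned a kit before. The two labels do not say clearly where such a person belongs:

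- If 'incident' means any later episode, habitual returners and people who have never returned a kit share one level.
- If it means previously screened, people who have never returned a kit fall in neither level.

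Earlier adequate return is the same behaviour as the primary outcome, measured before randomisation. Leaving it out costs power in the adjusted model. It also means the trial cannot show whether uptake rose among people who had never taken part or only among people who had taken part before. A later analysis plan could define 'incident', but it could not analyse a field that was never extracted.

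**Working it through.** **1. The plan's own figure.** Inputs from Sample size calculation: "The expected uptake of CRC screening in the control group (43.51" %), "The anticipated improvement in uptake in the intervention group (5 percentage points, to 48.51" %), and "with 80 % power and 5 % significance level, 1600 participants per trial arm are required". With p1 = 0.4351, p2 = 0.4851 and mean p = 0.4601, two-sided:

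n = [1.960·√(2·0.4601·0.5399) + 0.8416·√(0.4351·0.5649 + 0.4851·0.5149)]² / 0.05² = (1.3815 + 0.5925)² / 0.0025 ≈ 1559 per arm.

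The continuity correction, (n/4)·[1 + √(1 + 4/(n·0.05))]², gives 1599. The stated 1600 reproduces, and power at 1600 without correction is 81.0%. No covariate enters this calculation, so the coding of history does not affect it.

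**2. Assumptions about history (not in the documents).**
- Invitations are spread evenly over eight rounds: 1/8 first invitees, 7/8 repeat invitees.
- 43.51% of repeat invitees returned a kit before. The strata are then 0.125 first invitees, 0.875 × 0.4351 = 0.381 past returners and 0.875 × 0.5649 = 0.494 past non-returners.
- First invitees have control uptake of 43.51%. Past returners and non-returners have 60/30, 75/20 or 85/10 per cent.
- These give overall control uptake of 43.1%, 43.9% and 42.7%, close to the plan's 43.51%.
- One odds ratio applies in all strata, set so that overall uptake rises by 5 points.

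**3. Method.** In stratum s with n_s per arm and uptakes q0 and q1, v_s = 1/[n_s·q0(1−q0)] + 1/[n_s·q1(1−q1)]. The pooled log odds ratio has SE = 1/√Σ(1/v_s). Power = Φ(log OR/SE − 1.96).

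Worked for 75/20: n_s = 200, 609 and 791. The common log OR that lifts overall uptake from 0.439 to 0.489 is 0.2731, so intervention uptakes are 0.503, 0.798 and 0.247. The v_s are 0.0403, 0.0189 and 0.0147. Then Σ(1/v_s) ≈ 145.6, SE = 0.0829, z = 3.30 and power = Φ(1.34) = 0.91.

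**4. Results.**

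| Past returners / non-returners | Unadjusted log OR (SE), power | Three-level log OR (SE), power |
|---|---|---|
| 60 / 30 | 0.2017 (0.0711), 81% | 0.2191 (0.0741), 84% |
| 75 / 20 | 0.2012 (0.0710), 81% | 0.2731 (0.0829), 91% |
| 85 / 10 | 0.2020 (0.0711), 81% | 0.3989 (0.1006), 98% |

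The planned split, read as first versus any later episode, leaves power at 81% in every row.

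**5. Direction of the SE.** From the table, the SE grows by about 4%, 17% and 41% (0.0741/0.0711, 0.0829/0.0710, 0.1006/0.0711). The log OR grows by about 9%, 36% and 97%. Power rises because the conditional odds ratio moves away from 1 faster than its SE grows.

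**6. Other shares.** With 20% first invitees and 40% in each history group, calibrated to 43.51% overall, power is about 84% (59 vs 30 per cent), 89% (69 vs 20) and 97% (82 vs 8). The pattern is the same.

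**The case against.** The strongest reply is that nothing is broken. Allocation is individual, 1:1 and stratified by CCG, so the comparison of arms is unbiased without this covariate, and the sample size does not rely on it. That stands in full. A reader might infer that the trial is biased or too small; the documents support neither.

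Second, a reader might expect adjustment to narrow the reported interval. The linear-model formula 1 − √(1 − variance explained) would give SE reductions of about 4%, 14% and 29% in the three scenarios. That applies on the risk-difference scale. The plan reports logistic odds ratios, for which the SE rises. The gain is in power only, and the adjusted odds ratio is a different quantity from the univariable one.

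Third, it is tempting to call past response a strong and readily available predictor. The documents give no uptake by history and do not say that the Hub can supply it. Availability is plausible, because after non-response "the screening episode is closed (i.e. after 18 weeks) and the individuals practice receives a letter of notification regarding their non-participation", but it is an inference.

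Fourth, iPlato already identifies kit return by the end of week 7, before randomisation. That may be the better predictor, and adjusting for it would shrink the gain shown here by an amount the documents do not allow us to calculate. The Statistical analysis section does not list it as a covariate.

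Fifth, read with its label of episode number, 'incident' most naturally means any later episode, and a fuller protocol or SAP may say so. So this is an ambiguity, not a contradiction. But that reading is the one that pools opposite histories. The Hub's field list is introduced as a full statement of the added variables, not as examples, so defining the term would not supply the missing field.

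Finally, effect by past response is not among the stated aims. That is why only descriptive reporting is suggested.

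**Conclusion.** The point holds as a minor improvement. The stated covariate either merges past returners with past non-returners or leaves the latter uncoded, and the planned merge would not capture the difference. Across the assumed uptakes, a three-level covariate takes power in the multivariable model from about 81% to 84–98%; the univariable analysis is unchanged. The range rests on assumed shares, assumed uptake by history, a common odds ratio across strata and no adjustment for week-7 status. It also treats history as one earlier response, whereas the field proposed below is any earlier adequate screening, whose prevalence and predictive strength may differ. The figures show direction and plausible scale; they are not a forecast.

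**What to change.** Before the merge and anonymisation, ask the Hub to add one field: whether the person was adequately screened in any earlier episode, assuming its system holds this. In the multivariable model, replace the two-level covariate with three levels fixed at invitation:

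- first invitation;
- previously invited, never adequately screened;
- previously adequately screened.

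Report uptake by arm within these levels descriptively. If the field cannot be supplied, at least define 'incident' so that every participant has a category.

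The cost is one more anonymised field in an extract already planned and possibly a minor notification to the approving bodies, with no extra participants or contacts. The report should say that the adjusted odds ratio is conditional on history and not directly comparable with the univariable one.
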